#### **6.2.2 Blinding procedures**

Not applicable.

#### **6.2.3 Other methods of minimising bias**

In order to minimize bias block randomization will be used.

### **6.3 Unblinding Procedures (Code break)**

Not

applicable.

## 7. STUDY POPULATION

Healthy volunteers permanent residents in the Canton of St Gallen and employees at the Kantonsspital St. Gallen (excluding the personnel from the Division of Infectious Diseases and Hospital Epidemiology or Institute of Immunobiology) will be recruited. All the data regarding the study subjects will be collected in the Division of Infectious Diseases and Hospital Epidemiology. Analysis of participants' samples will be done in the Institute of Immunobiology KSSG and Institute of Microbiology from ETH Zürich.

### 7.1 Eligibility criteria

Participants fulfilling all of the following inclusion criteria are eligible for the study:

- Ability to understand the experimental nature of the vaccine evaluation and the patient informed consent form
- Written informed consent documented by date and signature to be obtained prior to any study specific procedure
- Age 18-50 years old
- Regular bowel movement (1+ defecation per day)
- Willingness to adhere to the strict timing schedule for the study evaluation
- Willingness to provide stool and blood samples in the indicated visits

The presence of any one of the following exclusion criteria will lead to exclusion of the participant:

- Previous use of an oral vaccine against *Salmonella* in the past 3 years
- Gastrointestinal infection caused by any *Salmonella* species during the past 3 years
- Positive HIV serology or any immune deficiency
- Current or planned pregnancy during the course of the study
- Unwillingness to use at least one method of birth control in women of childbearing age during the course of the study
- Breastfeeding
- Obstipation
- Hypersensitivity to any component of the vaccine or the enteric-coated capsule
- Use of an immune modulator in the past year
- Use of systemic corticosteroid treatment in the past 30 days
- Use of antibiotics within 1 week preceding and during the present study
- Current use of proton-pump inhibitors
- Participation in another study with investigational drug within the 30 days preceding and during the present study

### 7.2 Recruitment and screening

Participants will be recruited in the Division of Infectious Diseases and Hospital Epidemiology, Kantonsspital St. Gallen by PD [name]. Employees at the Kantonsspital St Gallen (excluding the personnel from the Division of Infectious Diseases and Hospital Epidemiology and Institute of Immunobiology) and permanent residents in the Canton of St. Gallen will be recruited. All the participants are independent of the persons involved in the trial. A flyer for the recruitment of participants will be submitted and approved by the EC, and will be used during the trial. New employers including medical students (Unterassistenten) will be informed during their entry examination by the Employee Health (Personalärztlicher Dienst) or during introductory sessions by

Human Resources.

At first, informed consent will be obtained. Participants will be allowed an appropriate period of reflection to ensure that informed consent is obtained through a communicative process. After participant consent, information regarding medical history and information used to apply inclusion and exclusion criteria will be collected. A physical examination and measurement of the vital signs to evaluate the overall health status of the study subjects will be made. Pregnancy and HIV tests will be performed at the beginning of the study. Blood samples will be collected and stored for evaluation of immunological parameters before the first vaccine dose administration.

Participants who fulfil inclusion criteria and are enrolled in the study will receive an inconvenience compensation of 50 CHF per study visit at the end of the study, which includes transportation costs.

### **7.3 Assignment to study groups**

Block randomization will be used in this study. Random number tables will be generated and assignments will be enclosed in sequentially numbered, opaque, sealed envelopes to designate the 15 subjects that will receive the vaccine and the 5 subjects that will not be administered. After assignment to vaccination/not vaccination groups, the participants will be informed in the second study visit to which group they belong by personnel from the Division of Infectious Diseases and Hospital Epidemiology, Kantonsspital St. Gallen.

### **7.4 Criteria for withdrawal / discontinuation of participants**

Study participants are withdrawn from the study in the following cases: a) withdrawal of informed consent, b) non-compliance and c) presence of SAE due to an unknown health condition of the participants or any other cause that compromise the integrity of participants.

## 8. STUDY INTERVENTION

### 8.1 Identity of Investigational Products (treatment)

#### 8.1.1 Experimental Intervention (treatment )

Vivotif® (Typhoid Vaccine Live Oral Ty21a) is a live attenuated vaccine for oral administration only. The vaccine contains the attenuated strain *Salmonella Typhi* Ty21a (1,2). Vivotif® is a commercial and Swissmedic-approved drug. It is manufactured by PaxVax Berna. The vaccine strain is grown in fermenters under controlled conditions in medium containing a digest of yeast extract, an acid digest of casein, dextrose and galactose. The bacteria are collected by centrifugation, mixed with a stabilizer containing sucrose, ascorbic acid and amino acids, and lyophilized. The lyophilized bacteria are mixed with lactose and magnesium stearate and filled into gelatin capsules which are coated with an organic solution to render them resistant to dissolution in stomach acid. The contents of each enteric-coated capsule are shown in Table 1.

---

*Table 1: Contents of one enteric-coated capsule of Vivotif® (Typhoid Vaccine Live Oral Ty21a)*

---

Viable *S. Typhi* Ty21a 2.0–10.0x10^9 colony-forming units\*

Non-viable *S. Typhi* Ty21a 5–50x10^9 bacterial cells

Sucrose 3.3 – 34.2 mg

Ascorbic acid 0.2 – 2.4 mg

Amino acid mixture 0.3 – 3.0 mg

Lactose up to 180 - 200 mg

Magnesium stearate 3.6–4.0 mg

\*Vaccine potency (viable cell counts per capsule) is determined by inoculation of agar plates with appropriate dilutions of the vaccine suspended in physiological saline.

---

#### 8.1.2 Control Intervention (standard/routine/comparator treatment )

Not applicable.

#### 8.1.3 Packaging, Labelling and Supply (re-supply)

The enteric-coated, salmon/white capsules of Vivotif® are packaged in 3-capsule foil blisters in a single package for distribution. Each package of vaccine shows an expiration date. This expiration date is valid only if the product has been maintained at 2 °C–8 °C (35.6 °F–46.4 °F).

The product used in the study will be obtained directly from the distributor Alloga AG, [name], [name] and will be kept at 4°C in a secured place in the study location. The study product will be labelled in accordance to Annex 13, Volume 4 of EUDRALEX and local regulatory requirements. The following label information will be added to each package of the product:

- a) Sponsor
- b) Patient identification number
- c) Study number
- d) Co-Investigator and study site

Unused vaccine: (Partly) unused or expired medication will be destroyed in the study site according to local guidelines but only after approval by the sponsor-investigator. The destruction shall be documented.

#### **8.1.4 Storage Conditions**

Vivotif® (Typhoid Vaccine Live Oral Ty21a) is not stable when exposed to ambient temperatures. Therefore it is shipped and stored between 2 °C and 8 °C (35.6 °F–46.4 °F).

### **8.2 Administration of experimental and control interventions**

#### **8.2.1 Experimental Intervention**

3 doses of the vaccine are to be administered in alternate days (0, 2 and 4). Vaccine potency is dependent upon storage under refrigeration [between 2 °C and 8 °C (35.6 °F– 46.4 °F)]. The vaccine should be stored under refrigeration at all times. One capsule is to be swallowed approximately 1 hour before a meal with a cold or lukewarm [temperature not to exceed body temperature, e.g., 37 °C (98.6 °F)] drink. Care should be taken not to chew the vaccine capsule. The vaccine capsule should be swallowed as soon after placing in the mouth as possible.

#### **8.2.2 Control Intervention**

Not applicable.

### **8.3 Dose / Device modifications**

Post-marketing surveillance has revealed that adverse reactions are infrequent and mild. Adverse reactions reported to the manufacturer during 1991–1995, time in which over 60 million doses (capsules) were administered included: diarrhea (N = 45), abdominal pain (N = 42), nausea (N = 35), fever (N = 34), headache (N = 26), skin rash (N = 26), vomiting (N = 18), or urticaria in the trunk and/or extremities (N = 13). One isolated, non-fatal anaphylactic shock considered to be an allergic reaction to the vaccine was reported. This adverse reactions show that the vaccine is relatively safe and therefore the expected adverse reactions will be infrequent and mild as described above.

Nevertheless in case of any SAE or in direct request from a participant to withdraw from the study, the vaccine administration will be stopped and the appropriate medication/treatment will be applied until the complete recovery of the study subjects.

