| Background and Rationale:    | 
Salmonella species are the most common bacterial pathogens causing gastrointestinal infection worldwide and represent a considerable burden in both developing and developed countries. Although Salmonella is an intracellular pathogen, B cells play a crucial role in the control and generation of immunity against this bacterium, as shown in pre-clinical studies. Likewise, the main mechanism that confers protection after application of the current licensed vaccines in humans is mediated by antibodies.
 
Outer membrane proteins (Omps), also known as porins, represent important targets of the protective antibody response against Salmonella in humans. Highly purified S. Typhi porins OmpC and F induce long-lasting IgM and IgG bactericidal antibody responses in mice and exhibit intrinsic adjuvant activity. Notably, patients recovering from typhoid fever present both IgG and IgM circulating antibodies against porins and a porin-based vaccine candidate based S. Typhi porins has been tested in humans resulting to be safe and immunogenic following subcutaneous application. The induction of porin-specific immune responses after vaccination with live attenuated Salmonella vaccine Vivotif® has not been assessed.
 
Moreover, the specific antigenic targets that mediate protection during vaccination have not been identified. In this open, interventional trial, healthy volunteers will be vaccinated with Vivotif® commercial Salmonella vaccine following the standard immunization scheme (three capsules taken orally, one every other day). Blood and stool samples will be collected before the first oral dose and at days 7, 21 and 56 after the intake of the last oral dose and immune responses against S. Typhi porins will be assessed.
 |

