In this open, randomised, interventional trial, healthy volunteers will be vaccinated with Vivotif® commercial *Salmonella* vaccine following the standard immunization scheme (three capsules taken orally, one every other day). Blood and stool samples will be collected before the first oral dose and at days 7, 21 and 56 after the intake of the last oral dose. Specific immune responses against *S. Typhi* porins will be assessed: a) IgM and IgG levels in serum and IgA in stool determined by ELISA, b) Flow cytometry analysis of porins-specific T and B cells from blood and c) Analysis of porins-specific B cells in blood by ELISpot. Additionally, the presence of mutants from the original inoculum administered will be analysed. For this, bacterial culture from stool samples will be performed and the genome of *Salmonella* will be sequenced to analyse mutations in the original sequences of the bacteria populations.

Altogether, this study not only will provide information about the immune responses elicited against *S. Typhi* porins during vaccination of healthy subjects with the commercial live attenuated vaccine Ty21a against *Salmonella Typhi*, but also will allow to characterize the behaviour of the bacterial populations of a live attenuated vaccine in humans. These studies are important due to the lack of information regarding the molecular changes that the bacteria experience during the infection in humans that allow their adaptation to the host and the continuous evolution and perpetuation of the disease.

As a final remark, Vivotif® has been shown to be safe; nevertheless some precautions will be taken in consideration during the study. The vaccine will not be administered during an acute gastrointestinal illness or in individuals receiving sulfonamides and antibiotics since these agents may be active against the vaccine strain and prevent a sufficient degree of multiplication to occur in order to induce a protective immune response. If persistent diarrhea or vomiting is occurring, administration will be stopped.

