### **Information for Participants**

It is essential that all 3 doses of vaccine are taken at the prescribed alternate day interval to obtain a maximal protective immune response. Vaccine potency is dependent upon storage under refrigeration [between 2 °C and 8 °C (35.6 °F– 46.4 °F)]. The vaccine should be stored under refrigeration at all times. It is essential to replace unused vaccine in the refrigerator between doses. The vaccine capsule should be swallowed approximately 1 hour before a meal with a cold or lukewarm [temperature not to exceed body temperature, e.g., 37 °C (98.6 °F)] drink. Care should be taken not to chew the vaccine capsule. The vaccine capsule should be swallowed as soon after placing in the mouth as possible.

Not all recipients of Vivotif® (Typhoid Vaccine Live Oral Ty21a) will be fully protected against typhoid fever. Travellers should take all necessary precautions to avoid contact or ingestion of potentially contaminated food or water. Several anti-malaria drugs, such as mefloquine, chloroquine and proguanil possess antibacterial activity which may interfere with the immunogenicity of Vivotif®. Clinical results indicate that mefloquine and chloroquine can be administered together with Vivotif®. Proguanil should be administered only if 10 days or more have elapsed since the final dose of Vivotif® was ingested. Any SAE related to the administration of the vaccine should be reported to a health care provider.

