## **8.6 Trial specific preventive measures**

The following preventive measures will be implemented:

- Assessment of participants' health and suitability to participate in the study before starting of the intervention by means of: a) pregnancy test, c) HIV test and c) Physical examination.
- Avoid the use of the following medications during the clinical trial: corticosteroids, immune modulators, antimitotic drugs, proton-pump inhibitors, sulphonamides, antibiotics and anti-malaria drugs, such as mefloquine, chloroquine and proguanil.
- Avoid taking the vaccine during an acute febrile illness or gastrointestinal illness and if persistent diarrhea or vomiting is occurring. Safety of the vaccine has not been demonstrated in persons deficient in their ability to mount a humoral or cell-mediated immune response, due to either a congenital or acquired immunodeficient state including treatment with immunosuppressive or antimitotic drugs.

Rescue medication: *Salmonella* gastrointestinal infections usually resolve in 5-7 days and most do not require treatment other than oral fluids. Persons with severe diarrhea may require rehydration with intravenous fluids. Choices for antibiotic therapy for severe infections include fluoroquinolones, third-generation cephalosporins, and ampicillin.

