### 10.1.3 Follow up of Serious Adverse Events

SAE will be reported from the moment starting the intervention until the end of the study to EC according to Swiss regulations. Participants terminating the study (either regularly or prematurely) with reported ongoing SAE, or vital signs being beyond the limit will be followed up until the end of the study (60 days after the administration of the first dose of the vaccine).

All SAE are collected, fully investigated and documented in the source document and appropriate CRF during the entire study period, i.e. from patient's informed consent until the last protocol-specific procedure, including a safety follow-up period. Documentation includes dates of event, treatment, resolution, assessment of seriousness and causal relationship to device and/or study procedure.

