### **11.4 Planned Analyses**

#### **11.4.1 Datasets to be analysed, analysis populations**

In the experimental group, all subjects who received all three doses of vaccine will be included in the study analysis.

All subjects randomized to the control group will be included in the analysis.

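### Response samples are defined from the last dose, but visit days are fixed from the first dose and differ between Table 1 and section 9.3; the rules for withholding or stopping vaccine are also unreconciled

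*Protocol*

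**What the plan says.** **Sampling times.** The Synopsis places the post-vaccination samples "at days 7, 21 and 56 after the intake of the last oral dose". Section 3.1 says the same, and sections 9.3.5 to 9.3.7 label Visits 5, 6 and 7 as 7, 21 and 56 days after the last immunisation.

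**Visit days.** The Study Schedule and Table 1 (section 9.1) put Visits 5, 6 and 7 on days 11, 25 and 60, each ± 1. Day 0 is the first dose; section 10.1.3 confirms the count by describing the end of the study as "60 days after the administration of the first dose of the vaccine". Section 8.2.1 gives the dosing days: "3 doses of the vaccine are to be administered in alternate days (0, 2 and 4". Those days carry no window. Sections 9.3.5, 9.3.6 and 9.3.7 are instead headed day 6, day 27 and day 60. Section 5.1 refers the reader to section 9.3 for the time points of the primary outcomes.

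**Analysis set.** In the vaccine group, section 11.4.1 states that "all subjects who received all three doses of vaccine will be included in the study analysis". It sets no condition on when the doses were taken.

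**Withholding or stopping vaccine.** Section 8.3: "Nevertheless in case of any SAE or in direct request from a participant to withdraw from the study, the vaccine administration will be stopped". Section 3.1: "If persistent diarrhea or vomiting is occurring, administration will be stopped"; the same section rules out a dose during acute gastrointestinal illness. Section 8.6: "Avoid taking the vaccine during an acute febrile illness or gastrointestinal illness and if persistent diarrhea or vomiting is occurring". Section 3.7 rules out a dose during acute febrile illness. Section 7.4 withdraws participants for an SAE, but qualifies the cause of the SAE. Section 3.2 adds "It is essential that all 3 doses of vaccine are taken at the prescribed alternate day interval".

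**The concern.** Every primary endpoint (serum IgM and IgG, stool IgA, porin-specific T and B cells) is read at Visits 5 to 7. Section 11.4.2 tests change from baseline within each group, and section 11.4.3 averages Visits 5 to 7 for the comparison with controls. Both treat a visit as a fixed time after vaccination. These responses change with time, so a sample taken at a different interval is not measuring the same quantity.

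The protocol gives staff two schedules for Visits 5 and 6. Neither says what happens to the later visits if the last dose is not taken on day 4. A change in dosing day would affect vaccinees only. The passages on withholding vaccine make an off-schedule dose conceivable, because wording that bars a dose during an illness can be read as a temporary hold. They are spread over five sections and do not give one consistent instruction.

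**Working it through.** **Inputs.** Doses on days 0, 2 and 4 (8.2.1). Targets 7, 21 and 56 days after the last dose (Synopsis, 3.1, 9.3). Visit days 11, 25 and 60, each ± 1 (Table 1). Visit days 6, 27 and 60 (headings of 9.3.5 to 9.3.7).

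**Step 1: reproduce Table 1.** Last dose day + target: 4 + 7 = 11, 4 + 21 = 25, 4 + 56 = 60. Table 1 is correct for on-time dosing.

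**Step 2: check section 9.3 with no delay.** Visit day − 4:
- Visit 5: 6 − 4 = 2 days, labelled 7 (5 days early).
- Visit 6: 27 − 4 = 23 days, labelled 21 (2 days late).
- Visit 7: 60 − 4 = 56 days, as labelled.

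Visits 5 and 6 are both outside ± 1 day. The last-dose days implied by the three headings and their labels are 6 − 7 = −1, 27 − 21 = 6 and 60 − 56 = 4. No single dosing day makes section 9.3 agree with itself.

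**Step 3: a late last dose with Table 1 days kept.** If the last dose is d days late, the interval to a visit on day v is (v ± 1) − (4 + d).

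| d | Visit 5 | Visit 6 | Visit 7 |
|---|---|---|---|
| 0 | 6–8 | 20–22 | 55–57 |
| 1 | 5–7 | 19–21 | 54–56 |
| 2 | 4–6 | 18–20 | 53–55 |
| 3 | 3–5 | 17–19 | 52–54 |
| 4 | 2–4 | 16–18 | 51–53 |

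With d = 1 the exact targets can still be met inside the window. With d = 2 they cannot; the best reachable intervals are 6, 20 and 55 days. From d = 3 no visit can come within 1 day of target. Counting from the actual last dose keeps 7, 21 and 56 for every d.

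**Step 4: dosing rules side by side.**

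| Condition | 3.1 | 3.7 | 7.4 | 8.3 | 8.6 |
|---|---|---|---|---|---|
| Persistent diarrhoea or vomiting | stop | – | – | – | avoid dose |
| Acute gastrointestinal illness | no dose | – | – | – | avoid dose |
| Acute febrile illness | – | no dose | – | – | avoid dose |
| SAE | – | – | withdraw, qualified by cause | stop, any SAE | – |

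The first row differs in its consequence: an end to administration in one section, avoidance of a dose in another, nothing in the dose-modification section. In the last row the SAE wording differs in scope. One section concerns leaving the study and the other stopping vaccine, so both can apply, but the text does not relate them.

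**The case against.** The case on the other side has real force.

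- **A reader might infer that the dosing rules contradict each other outright, so that section 8.3 would have a febrile participant dosed.** The text does not support this. Section 8.3 never says that its triggers are the only ones and gives no instruction about fever. Sections 3.7 and 8.6 agree that no dose is given during febrile illness. Nor would different sites act differently: the trial has one centre.
- **A reader might infer that any postponed dose spoils the samples.** A 1-day delay fits the ± 1 window. The protocol also never provides for postponement. If a dose barred by illness is simply lost, the vaccinee lacks three doses and drops out of the section 11.4.1 set, so no mistimed sample is analysed. The absence of a postponement rule would, on its own, be only missing detail.
- **A reader might put a probability on it from section 3.4**, which reports fever 3.3%, diarrhoea 2.9% and vomiting 1.5%. With 15 vaccinees the chance of at least one such symptom runs from 1 − 0.967^15 = 40% (complete overlap) to 1 − 0.923^15 = 70% (no overlap, 3.3 + 2.9 + 1.5 = 7.7%). That is not the chance of a delayed dose. These are overall symptom rates, not confined to the time before the third dose and not limited to acute febrile illness or persistent symptoms.
- **The target from the last dose is already written**, and staff could follow it rather than the table day. That is a fair reading, but nothing says which governs, and the window is attached to the table day.
- **The section 9.3 headings may be slips**, since the labels beneath them and both schedule tables agree. That is likely, but section 5.1 points to section 9.3, so the slips sit where the primary time points are looked up.

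**Conclusion.** The point holds in a limited form. The firm part needs no assumption about delays: sections 9.3.5 and 9.3.6 disagree with Table 1 and with their own labels, by 5 days at Visit 5 (day 6 against 11) and 2 days at Visit 6 (day 27 against 25). The conditional part is that visits counted from day 0 meet targets counted from the last dose only when that dose falls on day 4. If the last dose is given 2 or more days late and Table 1 days are kept, Visit 5 falls at most 6 days after it (4 to 6 for a 2-day delay), and section 11.4.1 still includes the participant. This assumes that a held dose may be given later, which the protocol neither allows nor forbids. Its frequency cannot be derived from the document. The relative effect is largest at Visit 5, since a 2-day shift is small against 21 or 56 days.

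Separately, the dosing passages are unreconciled on persistent diarrhoea or vomiting and on the scope of the SAE wording. They must be brought into agreement; which rule is right is not a statistical question.

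**What to change.** 1. In the Study Schedule, Table 1 and sections 9.3.5 to 9.3.7, define Visits 5, 6 and 7 as 7 ± 1, 21 ± 1 and 56 ± 1 days after the last capsule actually taken, with controls timed from their Visit 4. Remove the day 6 and day 27 headings. Days 11, 25 and 60 can remain as the expected days for on-time dosing. Record the actual dose dates in the eCRF so that the intervals can be checked.
2. Reconcile sections 3.1, 3.7, 7.4, 8.3 and 8.6 into one consistent statement on withholding and stopping vaccine, and refer to it from the other sections. The clinical team decides its content.

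The cost is wording and table edits, with no extra visits or samples. The one downside is that follow-up of a participant with a delayed dose ends later by the length of the delay.
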